### Excessive weight gain during pregnancy

Excessive weight gain in pregnancy is a common health-related problem in Western countries [3]. Women who gain excessive weight during pregnancy have an increased risk of postpartum obesity in themselves and their children [2,4]. Furthermore, 20% of women retain at least 5 kg of gestational weight gain at 6-18 months post birth [5,6], and this weight retention is a strong predictor of maternal overweight and obesity a decade or more after birth [7].

In 2009 the United States (US) Institute of Medicine (IOM) published revised guidelines for how much weight a woman should gain during pregnancy and highlighted the importance of intervention in pregnancy to prevent both postpartum weight retention and childhood obesity [8]. The US IOM recommends that women with a normal weight (Body Mass Index, BMI, of 18.5-24.9 kg/m^2^) should gain between 11-16 kg during their pregnancy; women who are overweight (BMI of 25-29.9 kg/m^2^) should gain 7-11 kg, and obese women (BMI of 30 kg/m^2 ^and above) should gain between 5 to 9 kg [8]. Women who are underweight (BMI less than 18.5 kg/m^2^) should gain between 13 to 18 kg during pregnancy [8]. Excessive gestational weight gain (GWG) is defined as weight gain above these recommended guidelines. The specific cost of excessive gestational weight gain is related to ensuing maternal health problems and fetal outcomes [9], such as preeclampsia [10], maternal hyperglycemia [11], complications with labor/delivery [12,13], infant macrosomia [12,13], late fetal death [14], birth defects [15], and an increased risk of caesarean [10].

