The Health Coaching Australia (HCA) Model [49] is an integrated Health Coaching model drawing on evidence-based psychological theories, practices and principles, such as Social Cognitive Theory [51], Readiness to Change, Importance, and Confidence [52], the Transtheoretical Model [53], and the Theory of Planned Behavior [54]. The HCA Model offers a unique intervention approach for preventing excessive gestational weight gain and weight retention in the postpartum because it provides behavioral, cognitive, situational, and emotional change facilitation: not just behavioral change facilitation [49].

We have developed a novel pregnancy HC intervention that has two components. (1) One-on-one sessions with a Health Coach that a) promote women's adoption of healthy lifestyle behaviors for the purpose of weight management, and b) address mood management and body image issues that commonly arise during pregnancy. (2) Educational group sessions, that augment the one-on-one sessions; the aim is to provide new mothers with additional information related to healthy behaviors and mood, and to support and assist them in initiating, maintaining, and achieving their goals for healthy behavior change.

### Specific aim 1

To compare the effectiveness of a specialized HC intervention during pregnancy, in preventing excessive gestational weight gain and postpartum weight retention 12 months post birth, compared to education alone. Hypothesis: In comparison to the education alone group, there will be a significantly greater proportion of women in the intervention group who: (1) will gain weight within the recommendations outlined by the American IOM [8] for gestational weight gain; (2) will have returned to their pre-pregnancy weight by 12 months post birth.

### Specific aim 2

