### Power, sample size, and retention

Given that the primary outcome of the study is maternal BMI, we aim to detect a clinically relevant difference in BMI of 0.8 kg/m^2 ^at 12 months postpartum. This difference is in accordance with the New Life (style) RCT that is currently being conducted in the Netherlands [63], that targets weight advice, weight development, nutrition and physical activity habits, but fails to target motivational variables, behavior-change assistance or psychological factors, such as depressive symptoms, anxiety symptoms, and body image. Consequently, the required *n *to detect this difference with 80% power at *α *= 0.05 and a standard deviation of 2 kg/m^2^, is 110 women per group; we have adopted this SD because we will also be measuring weight objectively at baseline and 12 months postpartum, removing any bias associated with self-report. Allowing for attrition of 20%, we will recruit 264 women and randomly assign 132 women into the HC Intervention and 132 women into the Education Alone control group. Our estimate of a drop-out rate is conservative and based on our previous large longitudinal studies with pregnant women and multiple time points [21,23,64]. As in our previous longitudinal pregnancy studies, this attrition rate of 20% takes into consideration that 5-7% of women may be diagnosed with gestational diabetes, which we expect to occur at 24-26 weeks; these women will therefore not affect the intervention, because we will over sample. A permuted blocks randomized treatment allocation schedule, produced by computer algorithm, will be used for the randomization process. To facilitate retention, we will build rapport with the participants through a study website, a regular newsletter, telephone support and advanced notification of assessments.

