### Analyses

We will adhere to 'intention-to-treat' principles following CONSORT Statement guidelines to prevent introduction of systematic bias [48]. As such, baseline data will be secured prior to treatment allocation, missing values will be scrutinized to check for non-random distribution and primary analyses will be executed twice: once using observed data, and once using multiple imputation under multivariate normal assumptions using methods given by Schaffer [65], so that all participants will be analyzed in their allocated condition. Analyses of covariance (with "other relevant variables" from above as covariates) will test the between group differences in the primary and secondary outcomes at each assessment time point and across time points. The confounder-adjusted analysis of the proportion of women returning to pre-pregnancy weight at 12 months post birth in each group will be tested using a logistic regression model. The second hypothesis will be tested using hierarchical regressions and path analysis. In addition, to further clarify the direction of effects between two variables across multiple time points, cross-lagged panel analyses will be conducted, e.g., to determine whether the level of maternal activity/depressive symptoms is a cause or consequence of higher BMI. Finally, the interview transcripts will be analyzed using elements of phenomenology and thematic content analysis to determine barriers to adopting healthy behaviors for weight management and the support or resources that women find most useful in achieving their gestational weight gain/postpartum weight loss goals [25,66].

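### Hypothesis 1(2), on 12-month weight retention, is decided by a yes/no cut with about 65% power, while the sized continuous analysis (about 84%) is neither linked to it nor stated to adjust for pre-pregnancy BMI

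*Protocol article*

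**What the plan says.** Specific aim 1 covers both gestational gain and retention at 12 months. Its hypothesis is about proportions of women. The second part is that more women in the coaching group "will have returned to their pre-pregnancy weight by 12 months post birth". The Analyses section gives the matching test: the "proportion of women returning to pre-pregnancy weight at 12 months post birth in each group will be tested using a logistic regression model", adjusted for confounders. No expected proportion, no tolerance around having returned, and no power is given for this test.

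The sample size rests on a different quantity. Power, sample size, and retention begins "Given that the primary outcome of the study is maternal BMI" and aims at a "clinically relevant difference in BMI of 0.8" kg/m² at 12 months. The stated requirement for "80% power at *α *= 0.05 and a standard deviation of 2 kg/m^2^, is 110 women per group".

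The Analyses section also plans analyses of covariance of the primary and secondary outcomes at each assessment, with the items listed under Other relevant variables as covariates. That list includes parity, socioeconomic status, social support and birth weight, among others. It does not include pre-pregnancy weight or BMI, although Measures says that pre-pregnancy BMI is collected at the first visit. The BMI subsection of Primary outcomes says that pre-pregnancy weight is self-reported and that 12-month weight is measured by researchers.

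**The concern.** Retention is a continuous quantity: 12-month weight minus pre-pregnancy weight, both of which the trial records. A cut at zero treats a woman 0.5 kg above her starting weight like one 10 kg above it, and so discards information. The article's background itself describes retention by degree: "20% of women retain at least 5 kg of gestational weight gain at 6-18 months post birth". The Institute of Medicine ranges that it cites concern gestational gain and do not supply a 12-month cut.

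At stake is the retention half of the primary aim. If the only test assigned to it is markedly weaker than the comparison used to size the trial, an effect that the plan calls clinically relevant could leave hypothesis 1(2) unsupported, simply because of how the outcome was scored.

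**Working it through.** **Inputs from Power, sample size, and retention.** Difference 0.8 kg/m², SD 2 kg/m², alpha 0.05 (two-sided assumed, since sidedness is not stated), 80% power, 110 per group. The standardised effect is 0.8/2 = 0.40.

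**The plan's own figure.** n per group = 2 × (1.96 + 0.842)² × 2² / 0.8² ≈ 98.1, so 99. The stated 110 is 11 higher. At 110 per group a two-sample t-test has 84.0% power (84.3% by the normal approximation). The stated number therefore gives somewhat more than 80% power for mean BMI. The check below uses 110.

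**Assumptions.**
- The 0.8 effect and SD of 2 carry over from BMI to retention in BMI units.
- Retention is normally distributed.
- Height is 1.65 m.
- The control distribution is placed so that 20% retain at least 5 kg, the background figure.

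**Placing the control group.** 5 kg at 1.65 m is 5/1.65² = 1.837 kg/m². The control mean is 1.837 − 0.842 × 2 = 0.153 kg/m².

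**Proportions returned (retention at or below zero).**
- Control: Φ(−0.153/2) = 0.469.
- Coaching: Φ((0.8 − 0.153)/2) = 0.627.
- Difference: 0.157 before rounding; mean proportion 0.548.

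**Power of the yes/no test at 110 per group.**
z = [0.1573 × √110 − 1.96 × √(2 × 0.548 × 0.452)] / √(0.469 × 0.531 + 0.627 × 0.373) ≈ 0.39, so power is Φ(0.39) ≈ 65%.

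| Women analysed per group | Continuous (t-test) | Yes/no cut | Loss (points) |
|---|---|---|---|
| 88 (110 less 20%) | 75% | 56% | about 20 |
| 105 (132 less 20%) | 82% | 63% | about 19 |
| 110 | 84% | 65% | about 19 |

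The cut needs about 156 per group for 80% power, against about 100 on the continuous scale. A simulation of 20,000 trials at 110 per group gave 83.8% for the t-test and 65.1% for the logistic Wald test. All these figures are without covariates.

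**Sensitivity.** Heights of 1.60 to 1.70 m change the cut's power by less than one point. With the control proportion varied freely at 110 per group, the normal approximation gives:

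| Control proportion returned | Power of the cut | Loss against 84.3% (points) |
|---|---|---|
| 15% | 53.9% | 30 |
| 30% | 63.7% | 21 |
| 40% | 65.4% | 19 |
| 50% | 64.7% | 20 |
| 70% | 56.8% | 28 |

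The loss is smallest near 40% and grows towards either end.

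**Do the extremes fit the article?** A control mean of 2.0 kg/m² (about 16% returned) implies 1 − Φ((1.837 − 2.0)/2) ≈ 53% retaining at least 5 kg. A mean of 1.2 kg/m² implies about 37%. Neither fits the 20% figure, so the supported size is about 19 points.

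**The case against.** The strongest reply is that the continuous comparison is already in the plan. Maternal BMI is the declared primary outcome, the sample size is for its mean, and ANCOVA is planned at each time point. Pre-pregnancy weight precedes randomisation, so its expected difference between arms is zero, and the expected difference in mean 12-month BMI equals that in mean BMI retention. With pre-pregnancy BMI as a covariate, ANCOVA of 12-month BMI and ANCOVA of retention give the same treatment coefficient. All of this stands. The cut does not weaken the sized comparison.

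A reader might infer that a large fall in retention that stops short of zero counts for nothing in this trial. The article does not support that: such a fall would count in the BMI ANCOVA and is lost only to the logistic test. A reader might also infer a loss approaching 30 points. That requires control proportions that do not fit the article's 20% figure.

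Two further replies have some force. The SD of 2 is justified by objective weights at 14-16 weeks and at 12 months, whereas retention uses a self-reported starting weight, so the absolute power for retention is uncertain. And the endpoint is not arbitrary: the background literature review describes an adequately powered trial that reported the percentage at or below preconception weight, and a percentage is easy to read. That is a good reason to report the proportion, but not to let it decide the hypothesis.

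What the replies leave open is the link. Nothing in the article says that the BMI ANCOVA answers hypothesis 1(2), and the stated covariates leave out the variable that would make it an adjusted analysis of retention. An analysis plan that is not shown might name that covariate, but the article itself fixes the proportion as the hypothesis and logistic regression as its test.

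**Conclusion.** The point holds in limited form. Hypothesis 1(2) is stated and tested only as a proportion. On the assumptions listed, that test would miss the plan's own target effect about 35% of the time at 110 per group, against about 16% on the continuous scale. The direction of the loss does not depend on the control proportion: no value tested at 110 per group gives less than about 19 points. The exact size does depend on carrying the BMI effect and SD over to retention and on the 20% background figure, so it is an illustration and not a property fixed by the article. The primary BMI comparison keeps its power. The change is worth making because it is specific and cheap, and because it would test the retention aim on the scale used to size the trial.

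**What to change.** In Specific aim 1 and Analyses, state that hypothesis 1(2) is decided by ANCOVA of 12-month BMI or weight (equivalently, of retention), with pre-pregnancy BMI or weight as a named covariate. Add that variable to the covariates under Other relevant variables. Keep the proportion returned to pre-pregnancy weight as a supporting result, reported by group with the difference and its confidence interval.

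The cost is wording only: no new data, visits or participants. There are two small downsides. A mean difference is less immediately readable than a percentage, which is why the percentage stays. And pre-pregnancy weight is self-reported, so any power quoted for retention should be labelled as an assumption.

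### Multiple imputation is stated only for the primary analyses, while secondary outcomes are tested by ANCOVA across time points, which ordinarily drops any woman missing a wave; the Aim 2 models have no stated missing-data method

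*Protocol article*

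**What the plan says.** The Analyses section of the protocol article opens with a commitment to intention-to-treat and says that missing values will be examined for non-random patterns. It then names one method for handling them and sets its scope: "primary analyses will be executed twice: once using observed data, and once using multiple imputation under multivariate normal assumptions". The stated purpose is "so that all participants will be analyzed in their allocated condition".

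The same section goes on to the models:

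- **Primary and secondary outcomes:** analyses of covariance, adjusted for the list under Other relevant variables, which "will test the between group differences in the primary and secondary outcomes at each assessment time point and across time points".
- **Aim 2:** "The second hypothesis will be tested using hierarchical regressions and path analysis".
- **Direction of effects:** "to further clarify the direction of effects between two variables across multiple time points, cross-lagged panel analyses will be conducted".

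No missing-data method is attached to the secondary outcomes or to the Aim 2 models.

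The only loss figure is in Power, sample size, and retention: "Allowing for attrition of 20%, we will recruit 264 women". That section calls the figure conservative and says that "this attrition rate of 20% takes into consideration that 5-7% of women may be diagnosed with gestational diabetes", so gestational diabetes is inside the 20% and not additional to it. The document gives no rate of missed questionnaires at individual waves.

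**The concern.** An ANCOVA across time points, fitted in the usual way to repeated measures or to their mean, needs every wave it uses. A woman who returns three of four follow-up questionnaires contributes nothing. There are four follow-ups (32 weeks gestation; 6 weeks, 6 months and 12 months postpartum), and the questionnaires are returned by post or completed by telephone, so some missed returns are foreseeable. For the primary analyses the imputed run compensates for this. For the secondary outcomes no such run is stated.

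Two things are at stake. The first is precision: women who were randomised and partly followed are discarded. The second is bias. The secondary outcomes include depressive symptoms, anxiety and body dissatisfaction, which the Background section links to weight gain. If women leave because of their mood or weight, and do so differently in the two arms, the complete-wave comparison no longer estimates the effect in all randomised women. The Aim 2 models draw on the same variables and carry the trial's claim about mechanism, so their handling of incomplete data matters too.

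**Working it through.** **The plan's own figures.** The stated inputs are a difference of 0.8 kg/m², SD 2 kg/m², 80% power and α = 0.05 (two-sided assumed), so d = 0.8/2 = 0.40.

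- n per arm = 2(1.960 + 0.842)²/0.40², which rounds up to 99 (100 by the t-test). The stated 110 is not reproduced; it gives about 84% power.
- The 132 per arm is 110 × 1.20. Dividing by the retained fraction gives 110/0.80 = 137.5, or 138.
- The number to be randomised is 264 in the sample-size section and 220 under Participants, so both are carried below.

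These are separate matters and are not relied on here.

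**Loss from a complete-wave model reaching 12 months.**

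- Documented input: 20% attrition, so the retained fraction is at most 0.80.
- Assumed input: a missed-return rate m at each of the three earlier follow-ups, independent across waves. The document gives no value, so a range is shown.
- Complete fraction = 0.80 × (1 − m)³.
  - m = 0: 0.800, loss 20%
  - m = 2%: 0.80 × 0.941 = 0.753, loss 25%
  - m = 5%: 0.80 × 0.857 = 0.686, loss 31%
  - m = 10%: 0.80 × 0.729 = 0.583, loss 42%

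**Detectable standardised difference** at 80% power, two-sided α = 0.05, from the two-sample t-test. The approximation (1.960 + 0.842) × √(2/n per arm) agrees to within about 0.003.

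| m | Complete of 264 | d | Complete of 220 | d |
|---|---|---|---|---|
| 0 | 211 | 0.387 | 176 | 0.425 |
| 2% | 199 | 0.399 | 166 | 0.438 |
| 5% | 181 | 0.419 | 151 | 0.459 |
| 10% | 154 | 0.454 | 128 | 0.498 |

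With 110 complete women per arm the figure is 0.379. Not all of the rise from there can be charged to discarding incomplete women, because no method recovers full information from women who have left.

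**How much a mixed model recovers.** This was simulated with 110 per arm and a true effect of 0.38 SD, comparing listwise ANCOVA with a mixed model on all available waves.

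- Precision: with about 70% complete, the standard error was 0.106 listwise and 0.098 mixed (ratio 1.08). With about 68% complete and a wave correlation of 0.5, it was 0.100 and 0.088 (ratio 1.14).
- Bias: when control-arm drop-out was made to follow the previous score, the listwise estimate fell to 0.28 in the first setting and 0.305 in the second. The mixed model gave 0.37 and 0.383.

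The bias figures depend on an assumed drop-out mechanism in one arm. They show what can happen and do not forecast this trial. No path or cross-lagged model was simulated.

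**The case against.** The strongest reply is that much of this could be inference from silence. A journal article condenses a fuller protocol, and the handling of missing data in secondary and mechanism models is commonly left to the analysis plan. Several parts of that reply stand.

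- **Aim 2.** A reader might infer that the regression, path and cross-lagged models run only on women with complete waves. The document does not say so. Path and cross-lagged models can be fitted by full-information likelihood or on imputed data, and a hierarchical regression needs only the waves it uses.
- **Per-time-point ANCOVAs.** These do not need the other follow-up waves. They do need their covariates, and the list under Other relevant variables includes birth weight and labor experiences, which a woman lost before delivery would lack.
- **Contradiction.** A reader might take the clause about analysing all participants as a promise covering every outcome. In context it gives the purpose of the imputed run of the primary analyses, so nothing is contradicted.
- **Size.** A loss of 30 to 40% might be inferred. On the formula above it requires about 4.4% to 9.1% missed returns at each of three waves, and the document supports neither figure. Its only loss figure is 20%, with the comment "Our estimate of a drop-out rate is conservative and based on our previous large longitudinal studies with pregnant women and multiple time points".

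The reply does not dispose of the secondary outcomes. There the article names both the scope of imputation and the method, and the named method, as ordinarily fitted across time points, discards partly observed women. Choosing a better method is not a request for missing detail.

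**Conclusion.** The point holds for the secondary outcomes tested across time points: the stated imputation does not reach them, and the stated method ordinarily excludes women with any missing wave. For Aim 2 it holds only in that no missing-data method is stated.

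The size supported by the document alone is a loss of about 20% from complete-case models that reach 12 months. Anything larger rests on assumed missed returns: 25% to 42% for 2% to 10% per wave at three waves, with a detectable d of about 0.40 to 0.45 (264 randomised) or 0.44 to 0.50 (220 randomised). In the simulations the avoidable part was a standard error 8% to 14% larger than the mixed model's.

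Bias is conditional. Loss unrelated to scores costs precision only; a material distortion of the arm difference needs drop-out that depends on earlier scores differently by arm. The primary analyses, which have an imputed run, are not affected by this point.

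**What to change.** In the Analyses section:

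1. For the secondary outcomes, replace ANCOVA across time points by a linear mixed model on all available waves, with arm by wave and the baseline value as covariate.
2. State that the Aim 2 regression, path and cross-lagged models will be fitted by full-information maximum likelihood, or on the imputed data sets already planned. In the second case the imputation model must include the Aim 2 variables.
3. Keep the complete-case versions as sensitivity analyses.

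The cost is a few sentences and slightly more programming, with no extra women or data. The downside is reliance on missing at random: if drop-out depends on unobserved scores, these methods can be biased too, and the complete-case comparison will not settle that.

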## Methods/Design

### Overall study design

This study will be a randomized controlled trial (RCT) with pregnant women randomly allocated to either the HC Intervention or an Education Alone control group. The study will be conducted and reported in line with CONSORT recommendations [55]. Baseline assessment of study variables will occur at 14-16 weeks gestation; this allows women to consider the pregnancy certain (since the threat of miscarriage has substantially decreased) and to participate at a standardized time point. Follow up assessments will take place at 32 weeks gestation, and at 6 weeks, and 6 and 12 months postpartum. The study was approved by the Eastern Health Human Research Ethics Committee on the 25th March, 2011 (EH-HREC E40/1011) and Deakin University Human Research Ethics Committee on 21st April, 2011 (DUHREC 2011-087).

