### Measures

Women will meet with researchers at 14-16 weeks gestation to collect demographic information (including pre-pregnancy BMI) and obtain anthropometric measurements (BMI and waist circumference). Women will also be given a copy of the US IOM gestational weight gain guidelines [9] and baseline measures of motivation, importance, confidence and readiness to adopt healthy lifestyle behaviors for weight management, perceived social support, depressive symptoms, body dissatisfaction, dietary habits and physical activity will be collected by questionnaire. Follow-up assessment of measures will take place at 32 weeks gestation, and at 6 weeks, 6 and 12 months post birth, with the exception of anthropometric measures which will be assessed at baseline and at 12 months post birth.

All measures in the questionnaire, with the exception of the first 14-16 week assessment session, will be collected in one of two ways: (1) via self-report questionnaires sent to the home of women with a request to return completed questionnaires (that will take no more than 30 minutes to complete) to the researchers in reply-paid envelopes provided to them; (2) by researcher interview over the phone. Women will be able to choose the method of data collection that suits them best. Anthropometric measures will be obtained in person by trained research staff.

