### Primary outcomes

#### BMI

Height will be measured by researchers with a stadiometer at the first and last assessments (14-16 weeks gestation and 12 months postpartum) for both groups. Women will be weighed each time wearing light clothing and no shoes. Pre-pregnancy weight will be based on self-report; weight at 14-16 weeks gestation and 12 months postpartum will be measured by the researchers using electronic scales. Height and weight measurements will be used to calculate BMI (kg/m^2^). At all other assessment time points, women will be encouraged to consult with their healthcare professional to provide additional objective weight measurements (including the last weight reported prior to delivery), and in the postpartum we will ask women to be weighed at their Maternal and Child Health appointment. Women will record these measurements in a 'weight passport' provided by researchers.

Waist circumference will be measured by trained researchers using a standard tape measure when height and weight measurements are obtained.

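### The supplementary cross-lagged analysis is said to settle whether activity or depressive symptoms cause or follow higher BMI; it can show only temporal association, and researchers measure BMI at just two of the five waves

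*Protocol article*

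**What the plan says.** The Analyses section of the protocol article assigns the second hypothesis to hierarchical regressions and path analysis. It then adds a further step: "to further clarify the direction of effects between two variables across multiple time points, cross-lagged panel analyses will be conducted". The example given is "to determine whether the level of maternal activity/depressive symptoms is a cause or consequence of higher BMI". No assumptions for a causal reading accompany it.

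There are five assessment waves: a baseline at 14-16 weeks, and then, under Overall study design, "Follow up assessments will take place at 32 weeks gestation, and at 6 weeks, and 6 and 12 months postpartum". The questionnaire measures are collected at all of them. BMI is treated differently. The Measures section lists the follow-up waves "with the exception of anthropometric measures which will be assessed at baseline and at 12 months post birth", and the BMI section agrees: "weight at 14-16 weeks gestation and 12 months postpartum will be measured by the researchers using electronic scales". For the remaining waves, "At all other assessment time points, women will be encouraged to consult with their healthcare professional to provide additional objective weight measurements", and "Women will record these measurements in a 'weight passport' provided by researchers". After birth, women are asked to be weighed at their Maternal and Child Health visit.

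**The concern.** The text names both a method and the conclusion it is meant to deliver, and the method does not deliver that conclusion. A plain cross-lagged regression adjusts for the outcome's previous value, but that single value captures a woman's stable level only imperfectly. If heavier women tend to be more depressed or less active for lasting reasons, and neither variable acts on the other, the uncaptured part appears as a lagged path. If one variable is more stable than the other, the two directions are inflated by different amounts. That asymmetry is what would be read as cause in one direction and consequence in the other.

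The BMI series adds to the difficulty. Analysis over several time points must join two researcher-measured values to three obtained another way. The first two waves also fall in pregnancy, when BMI includes the weight of the pregnancy.

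At stake is a causal statement about mechanism in a trial whose authors expect it to inform practice and policy. The randomised comparison of weight outcomes is not at stake.

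**Working it through.** **BMI waves.** Five waves are planned: 14-16 weeks, 32 weeks, 6 weeks, 6 months and 12 months. Researchers measure weight at the first and last, so 2 of 5. Two waves give one lag, from early pregnancy to 12 months after birth. A random-intercept cross-lagged model needs at least three waves, so it depends on the passport weights.

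**False-positive rate with no effect in either direction.** The plan gives no figure to reproduce. This is an illustration.

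Input derived from the article: 264 women recruited with 20% attrition (Power, sample size, and retention) gives 264 × 0.80 = 211.

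Assumed inputs: each standardised score is a stable trait plus a changing state. The trait share is 0.5 for symptoms or activity (X) and 0.8 for BMI (Y). State autocorrelation between waves is 0.3. The states of X and Y are independent, and the traits correlate ρ.

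Formulas:
- Correlation of X and Y at any lag: c = ρ√(0.5 × 0.8)
- Stability of BMI: 0.8 + 0.3 × 0.2 = 0.86. Stability of X: 0.5 + 0.3 × 0.5 = 0.65
- Cross-lagged path, with r the outcome's stability: b = c(1 − r)/(1 − c²)
- R² = r² + c²(1 − r)²/(1 − c²)
- SE = √[(1 − R²)/((1 − c²)(n − 3))]
- Rejection rate = P(Z > 1.97 − b/SE) + P(Z < −1.97 − b/SE)

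At ρ = 0.3, c = 0.3 × √0.40 = 0.190 and 1 − c² = 0.964.
- X to BMI: b = 0.190 × 0.14/0.964 = 0.0276; R² = 0.740; SE = √(0.2597/(0.964 × 208)) = 0.0360; b/SE = 0.77; rejection 0.114 + 0.003 = 12%.
- BMI to X: b = 0.190 × 0.35/0.964 = 0.0689; R² = 0.427; SE = √(0.5729/(0.964 × 208)) = 0.0535; b/SE = 1.29; rejection 25%.

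| Trait correlation ρ | X to BMI | BMI to X |
|---|---|---|
| 0 | 5% | 5% |
| 0.1 | 6% | 7% |
| 0.2 | 8% | 13% |
| 0.3 | 12% | 25% |
| 0.4 | 18% | 41% |

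**Sensitivity.** With equal trait shares of 0.5, 0.65 and 0.8 for both variables and ρ = 0.3, the same formulas give 16% to 19%, with no difference by direction. Simulation with 220 women and measurement error in both scores gave 10% to 15% for symptoms to BMI and 25% to 30% for BMI to symptoms at ρ = 0.3. If BMI is almost wholly stable (trait share 0.95), the path into BMI is significant in only about 6% to 7% of trials, but the path from BMI to symptoms remains near 30%.

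**The case against.** The strongest reply is about scope. The sentence is an example within an added analysis. Aim 2 is tested mainly by hierarchical regressions and path analysis, and its hypothesis is a contrast with education alone. That stands: a reader might infer that Aim 2 as a whole would report causal direction from these paths, and the article does not support that reading.

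Second, a condensed article may leave model form to an analysis plan, and random intercepts might already be intended. That also stands. Not naming the model is no fault, and the rates above apply to the plain model only. It does not rescue the stated conclusion, however. Even a random-intercept model removes only stable confounding, and the causal claim is written in the article itself.

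Third, the size depends on assumptions. At ρ = 0.1 the inflation nearly vanishes. It is tempting to take scale from the correlations of .23 to .46 under Determinants and correlates of gestational weight gain, but those relate body dissatisfaction to depressive symptoms. It is also tempting to quote the chance that at least one of four lags is significant. That chance is already 18% to 20% with uncorrelated traits, through multiplicity alone, so only single-path rates are used here.

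Fourth, a reader might infer that mid-study BMI is missing or self-estimated. It is neither: health professionals are meant to take the weight, and the woman records it. Mixed sources and pregnancy weight are limitations of the series, not contradictions in the plan.

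**Conclusion.** The point holds in limited form. The article promises a causal conclusion that lagged paths between non-randomised variables cannot give without strong assumptions it does not state: no stable or unmeasured common causes, a suitable lag, and comparable measurement across waves. With about 211 women, trait correlation 0.3 and trait shares of 0.5 to 0.8, a plain cross-lagged path is significant in about 12% to 25% of trials when nothing causes anything, and the rate can differ by direction. At correlation 0.1 it is about 5% to 7%. The true correlations of BMI with depressive symptoms or activity are not given, so these rates illustrate the risk and do not estimate it. The count of two researcher-measured BMI waves out of five is correct. This should be corrected, but it concerns a supplementary analysis and leaves the randomised primary comparison untouched.

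**What to change.** - Replace the cause-or-consequence wording with temporal association, and keep causal statements for the randomised contrast.
- Fit a random-intercept cross-lagged model, at least as a sensitivity analysis, for women with three or more waves of weight. It separates stable differences between women from change within a woman.
- Mark passport weights as a different source from researcher-measured weights, and state which source feeds each wave.

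No new data are needed. The cost is some rewording and a somewhat larger model. The lagged paths will have wider intervals, the claim will be weaker, and the random-intercept model will depend on how many women return passport weights.
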